#### Participant HCWs exclusion criteria

Age < 18 years old

#### Who will take informed consent? {26a}

Individuals who agree to participate and who meet the study eligibility criteria will then be invited to an in person meeting to learn about the study and to provide written informed consent. Participants’ names will not be written on used questionnaires and schedules and no record of participants’ names will be kept. Interviews will be conducted with the strictest confidentiality at an appropriate location without any disruption in the services provision.

#### Additional consent provisions for collection and use of participant data and biological specimens {26b}

On the consent form, participants will be asked for their consent to the use of their data in the event of their withdrawal from the trial. Participants will also be requested to grant permission for the research team to share relevant data with individuals affiliated with the participating Universities or regulatory authorities, where applicable. This trial does not involve the collection or storage of any biological specimens.

## Interventions

### Explanation for the choice of comparators {6b}

The comparator will be the current standard of care, which does not include any approach to the management of aggressive or violent behavior by HCWs. The trial will compare within each cluster the incidence of violent episodes and their severity before the introduction of the de-escalation of violence training and the code of conduct with the incidence of violent episodes and their severity from health facilities, after the intervention deployment. The SW-RCT design allows each site to serve as its own control and likely reduces the potential for confounding on cluster and possibly individual-level characteristics.

### Intervention description {11a}

The intervention consists of two key components, (1) an individual capacity building component delivered through a de-escalation of violence training for HCWs and (2) a code of conduct delivered via a warning board to be implemented at the health facilities and co-developed during the formative phase. HCWs will also receive a refreshment training. The de-escalation of violence training program developed by the ICRC will be used for the implementation [39]. The training will be delivered to HCWs in participating clusters over a half-day workshop. Expert physicians from the MoH and from the research teams from the collaborating universities will co-facilitate the group sessions. The de-escalation of violence training is designed to provide HCWs with the ability to identify tense situations from the outset and to develop skills to defuse them before they further escalate. Furthermore, the training helps to improve the communication skills of HCWs with patients and their families. The training will consist of five modules: (1) an introductory module, (2) understanding violence in health-care settings: causes and effects, (3) learning key behaviors for preventing and de-escalating tense situations, (4) communicating and engaging with people, and (5) taking learning back into the workplace [39]. The training is based on behavioral theory, which states that people learn new behaviors more effectively when their needs are analyzed in a way to ensure their usefulness and applicability. The learnt behaviors provide a direct benefit to the participants when the techniques are practiced during the training. The training material will be contextualized and adapted to include real case-scenarios highlighted during the formative research phase. Once a group of clusters crosses over into the intervention phase, trainers will start the delivery of the training according to a pre-defined delivery schedule (Fig. 1). All HCWs who meet the inclusion criteria will start the training. Along with the de-escalation of violence training, a code of conduct developed during the formative phase will be introduced and displayed in the participating clusters, according to the rollout process.

### Criteria for discontinuing or modifying allocated interventions {11b}

Participants will be informed that they are free to withdraw their consent and that they can reject further participation in the trial at any time.

### Strategies to improve adherence to interventions {11c}

Each health facility will designate a contact person who will be supportive of the violence de-escalation implementation. Hospital managers will also be involved in providing their support by participating in the training and providing ongoing feedback to HCWs adhering to the intervention. Further, peer support among HCWs will be encouraged through group discussions and case presentations to help them implement the violence de-escalation intervention.

### Relevant concomitant care permitted or prohibited during the trial {11d}

The interventions are designed to change the behaviors that HCWs and clients take with regard to violence against health care. They neither require nor preclude concomitant care during the trial.

### Provisions for post-trial care {30}

Participants in the trial will be allowed to receive care if needed.

### Outcomes {12}

#### Endpoints of study phase 2 (stepped-wedge cluster randomized controlled study)

Primary endpointsNumber of physical and non-physical incidents (verbal abuse, threats, ironic language, provocative or aggressive body language, etc.) reported during the fulfilment of a professional activity in the last 6 months;Secondary endpoints

Type of violenceNumber of physical and non-physical incidents reported by type, by perpetrator, by place, by time, by gender, and during the fulfilment of which activity in the last 6 months;

Coping with violenceLevel of communication skills related to workplace violence among HCWs [40];Clinician Confidence in Coping With Patient Aggression (CCPAI scale) [34]

Psychological endpointsLevel of post-traumatic stress disorders (PTSD) among HCWs (PTSD Checklist for DSM-5) [41–43];Level of burnout among HCWs (Maslach burnout inventory scale) [44, 45];Psychological empathy among HCWs (Jefferson scale of physician empathy scale) [40, 46, 47];Job satisfaction

Organizational endpointsNumber of sick leave spells taken during the study period;Intent to leave among HCWs because of violence (TIS-6 Intention to leave scale) [48, 49]

### Participant timeline {13}

#### Sample size {14}

Power simulations were performed separately for the study in Iraq and the study in DRC based on the study design scheme given in Table 1. Details of the simulations are provided in an online supplement (see Supplementary file 1). For short, the average number of events per HCWs and 6-month period was assumed to be 1 without intervention, 0.6 after intervention B, and 0.6 in the 6-month period following interventions I and R. A relapse to 0.7 was assumed for the effect of intervention I in the second period after intervention in arms 1, 4, and 7. All effects were assumed to be additive on the log-scale of expected event numbers. We further assumed average event rates to vary between facilities and between HCWs within facilities. Both variations were assumed to follow a normal distribution on the log scale of expected event numbers, with a mean value of 0 and a standard deviation of 0.2. We assumed the probability of a HCW quitting in a given period to be at most 30%. Under these assumptions, 22 health facilities in Iraq with 12 HCW per facility and 33 health facilities in DRC with 5 HCW per facility would provide more than 90% power for finding statistically significant effects of interventions B and I after pooling results from the two countries, assuming a significance level of 5%. The power to detect a significant effect of intervention R after pooling would also exceed 90% if quitting HCWs are replaced one by one.

**Table 1 Tab1:** Participant timeline

			Study periods						
	Allocation		Post-allocation						Close-out
	P1 *0–12 weeks*		P2 *13–37 weeks*		P3 *38–62 weeks*		P4 *63–87 weeks*		*88–99 weeks*
Time points	0	Bas.		FU1		FU2		FU3	
Recruitment									
Eligibility screen	x								
Informed consent	x								
Demographic data	x								
Allocation	x								
Assessments									
Aggression log (continuous)	x		x		x		x		
Health care staff questionnaire		x		x		x		x	
Level of confidence (CCPAI self-efficacy)		x						x	
PTSD Checklist for DSM-5 (PCL-5)		x		x		x		x	
Level of burnout (Maslach burnout inventory scale)		x		x		x		x	
Jefferson physician empathy scale		x						x	
TIS-6 Intention to leave		x		x		x		x	
EQ-5D-5L (EuroQol 5 Dimension 5 Level) Quality of life (QoL)		x		x		x		x	
Assessment of costs		x		x		x		x	
Data analysis and reporting							x		x

Table 2 describes the expected total number of HCWs that will be recruited per country to allow for 10, 20, and 30% drop outs within the 6-months period.

**Table 2 Tab2:** Results of the power simulations (500 replications). Estimated Power to detect a significant effect of the respective intervention at the 5%-level, if quitting HCWs are replaced at the beginning of the next study period

	Iraq			DRC			Summary estimate		
Probability of quitting in a given period	10%	20%	30%	10%	20%	30%	10%	20%	30%
Intervention I (individual training followed by collaborative learning)	0.98	0.98	0.97	0.94	0.90	0.89	0.99	0.99	0.99
Board intervention B	0.97	0.97	0.95	0.89	0.87	0.89	0.99	0.99	0.99
Refreshment intervention R	0.73	0.70	0.68	0.60	0.54	0.54	0.92	0.90	0.89

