Successively, secondary outcomes will be measured on the same individuals, from each cluster at discrete point in time using standardized and validated questionnaires and scales. The total length of the study trial will vary across arms. HCWs from arms with the longest trial duration will have four discrete outcome measurements taken, i.e., at baseline, during the last 2 weeks of P1, at 22 weeks after the intervention introduction, at the end of observation period 2 (P2) (first follow-up FU1), at 47 weeks at the end of P3 (FU2), and at 72 weeks from the intervention, at the end of P4 (FU3) (Fig. 1). These arms will have an overall trial duration of 87 weeks. Arms with shorter durations will have fewer outcome measurements taken. Data collection tools will be programmed electronically on tablets, using Open Data Kit (ODK) [51]. The questionnaire will be administered in French in DRC and in Arabic or English in Iraq and will include questions about HCWs exposure to violence, either to physical or verbal violence, the immediate actions taken if any after being exposed to violence, whether they reported the violence, or if any action was taken by the authorities. Questions will also inquire about family members’ or colleagues’ exposure to any sort of violence and the perspective of the participants about the future of this phenomenon. The questionnaire will also include validated scales to assess different psychosocial variables as for example, post-traumatic stress disorders (PTSD), the level of burnout, or measures of quality of life and cost data (see Table 3 Participant timeline).

**Table 3 Tab3:** Sample size

	Iraq			DRC		
Drop out probability within an observation period	10%	20%	30%	10%	20%	30%
Expected number of health care workers to be recruited	340	415	491	212	259	307

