## Statistical methods

### Statistical methods for primary and secondary outcomes {20a}

Descriptive statistics will be used to summarize the characteristics of HCWs. For the analysis of observed event data, the model applied with the simulated data sets will again be used. HCWs will be considered as separate observational units. For each observation period, the time during which a HCW was under observation will be used as individual offset variable and each HCW will get his/her own random intercept in the analysis. Additional analyses will involve scores reported by the HCW at the end of each period or even during periods. Mixed linear models with robust standard error estimates involving analogous terms as the mixed Poisson regression models will be used; however, without accounting for the time, a HCW has been active during a given period. Analyses addressing the occurrence of severe events will be conducted using mixed logistic regression models. In this case, the outcome is 1 if the respective health worker experienced a severe event in the respective period and 0 otherwise. The structure of these models will be analogous to the one of the models for event rates and scores.

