## Discussion

Violence against health care is a global emergency, particularly in fragile contexts. Research on the patterns and motivations of violence in post-crisis settings from the Africa and Middle East regions is scarce. This study will adopt a stepped-wedge cluster randomized controlled trial design to investigate the impact of a contextualized de-escalation of violence training for health care workers (HCWs) and of a co-designed code of conduct for both clients and HCWs at the level of the health facilities, on the incidence and severity of both verbal and physical violent episodes in two post-conflict settings, the Democratic Republic of Congo (DRC) and Iraq. Strengthening social accountability by involving communities in researching causes of violence against HCWs and in designing solutions will enhance the appropriate understanding of cultural and social factors behind the motivations of violence in these settings, and most importantly, communities will become advocates for a sustainable intervention. Thus, the bottom-up crafting of rules for the code of conduct will enhance acceptability and sustainability of the intervention and will allow contextualizing the trainings on de-escalation of violence for HCWs. Following the participant longitudinally during the SW-RCT will yield a comprehensive understanding of the effect of the de-escalation violence training in isolation or in combination with the code of conduct on the incidence and severity of episodes of violence and whether the adapted de-escalation violence training would prevent violence in the early stages. At the same time, the strong research methodology will be essential in identifying the most (cost-) effective way to implement interventions in urban and rural areas in these contexts. Further, it is also expected that the intervention will have an impact on specific outcomes measured through the CCPAI and MBI score or the Physician Empathy scale, meaning that the adapted de-escalation training is expected to also contribute to increased confidence, less burnout, and increased empathy among HCWs.

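### The CCPAI confidence and Jefferson empathy scales are scheduled only at baseline and FU3; unless some arms are still untrained at FU3, their training effect is a before/after comparison confounded with calendar time

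*Protocol article*

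**What the plan says.** Table 1 (under Sample size {14}) has four questionnaire visits: Bas., FU1, FU2 and FU3. The row beginning "PTSD Checklist for DSM-5 (PCL-5" has a mark at each of them, as do the burnout, TIS-6 and EQ-5D-5L rows. The rows "Level of confidence (CCPAI self-efficacy" and "Jefferson physician empathy scale" have marks at Bas. and FU3 only.

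Both scales are named secondary endpoints of phase 2. The endpoint list has an entry beginning "Clinician Confidence in Coping With Patient Aggression (CCPAI scale" and lists the Jefferson scale among the psychological endpoints.

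Section {18a} places baseline in the last two weeks of P1, the initial 12-week observation period. For the arms with the longest duration, the final visit is "at 72 weeks from the intervention, at the end of P4 (FU3". For the others it says only: "Arms with shorter durations will have fewer outcome measurements taken".

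For scores reported at the end of each period, section {20a} states: "Mixed linear models with robust standard error estimates involving analogous terms as the mixed Poisson regression models will be used".

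The Discussion adds that "the adapted de-escalation training is expected to also contribute to increased confidence, less burnout, and increased empathy among HCWs".

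**The concern.** A stepped-wedge trial learns about its intervention mainly from visits at which some clusters have crossed over and others have not. In a rollout of this kind those visits are FU1 and FU2, and these two scales skip both. At baseline no facility is trained. If all are trained at FU3, the training indicator and the FU3 period indicator are the same column. The model of section {20a} then cannot tell a training effect from anything else that changed between the two visits.

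In the longest arms the two visits lie about 75 weeks apart (week 12 to week 87). The Iraqi participants are first-year residents, whose confidence and empathy may well change over that time without any training. Staff turnover and changes in local security could also move the scores. All of this would be read as a training effect, on endpoints for which the Discussion expects a benefit.

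**Working it through.** **Timeline.** Table 1 ends P2, P3 and P4 at weeks 37, 62 and 87. Section {18a} puts FU1, FU2 and FU3 at 22, 47 and 72 weeks after introduction in the longest arms. The differences are 37 − 22 = 62 − 47 = 87 − 72 = 15. The figures agree with each other, and the longest arms are trained in week 15, early in P2. Baseline (end of P1, week 12) is before that.

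**Training status at FU3.** The Trial design section has clusters moving from control to intervention in random order. The section on comparators has each site serving as its own control. Together these imply that every site crosses over. Status by arm in P4 is not stated in the text; it belongs to Fig. 3, which is not available here. Both cases are therefore worked through.

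**Model.** Arm-level means for 11 arms, with 11 arm effects, one effect per visit after baseline, and a training indicator (0/1). Variances are in units of the residual variance of one arm mean. The rollout of 4, 4 and 3 arms in P2, P3 and P4 is an assumption.

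*Case A: all arms trained by FU3.*
- Bas. and FU3 only: 11 + 1 + 1 = 13 columns, rank 12. The training effect is not estimable apart from the period effect. This does not depend on the 4/4/3 split, only on all arms being untrained at baseline and trained at FU3.
- All four visits: 11 + 3 + 1 = 15 columns, rank 15. The sum of squares of the training indicator after removing arm and visit means is 23 − 13.75 − 18.27 + 12.02 = 3.00, so the variance is 1/3.00 = 0.33.
- If only some arms (assumed 4 of 11) have an FU3: rank 12 of 13.
- If shorter arms take the scales at their own last visit, and all arms are trained by then (assumed trained in P2): rank 14 of 15. The effect is still not estimable.

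*Case B: k arms still untrained at FU3.* With two visits the estimator is a difference of changes between 11 − k trained and k untrained arms, with variance 2 × [1/k + 1/(11 − k)]. The four-visit comparison keeps the assumed rollout and leaves k of the last three arms untrained.

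| k | Two visits | Four visits | Ratio |
|---|---|---|---|
| 1 | 2 × (1 + 1/10) = 2.20 | 0.32 | 6.9 |
| 2 | 2 × (1/2 + 1/9) = 1.22 | 0.32 | 3.8 |
| 3 | 2 × (1/3 + 1/8) = 0.92 | 0.33 | 2.8 |

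So the effect becomes estimable as soon as one arm is untrained at FU3, but at roughly 3 to 7 times the variance.

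**Adding FU2 alone.** With Bas., FU2 and FU3 in Case A there are 11 + 2 + 1 = 14 columns, rank 14. The variance is 1/(19 − 11.67 − 16.82 + 10.94) = 1/1.45 = 0.69. One visit in mid-rollout restores estimability, at about twice the variance of the full schedule.

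**Text against table.** Section {18a} gives the longest arms four measurements of the secondary outcomes and makes no exception for any scale. Section {20a} analyses scores from the end of each period. Table 1 does not supply such data for these two scales.

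**The case against.** The strongest objection is that the premise is not on the page. A reader might infer that no untrained facility is left at FU3, that the effect is therefore fully confounded, and that shorter arms never reach FU3 and so give no value after baseline. The documents support none of these as a statement of fact. The figure with the arm-by-period scheme is not available, and the 72-week timing is given only for the longest arms. Section {18a} does not say which visits the shorter arms omit, or whether they take these scales at their own last visit. The design also combines training, refresher and board over 11 sequences, so arms may differ at FU3 in board, refresher or time since training. Some randomised information on those components may survive. This objection stands, and the point has to be conditional. It does not remove the defect: with one to three arms untrained, training versus none is still poorly estimated, and the other contrasts do not answer that question.

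A second objection is that little depends on it. The secondary objectives speak of assessing levels rather than effectiveness, and the Discussion sentence is an expectation, not a confirmatory claim. That limits the severity. The sentence is still causal, and section {20a} proposes the effect model for such scores.

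A third objection is that it may be too late to change the schedule. Trial status gives August 2023 as the target completion, and the article appeared in December 2023. Yet recruitment began in November 2022. If week 0 fell in that month, week 62 would fall in January or February 2024 and week 87 in July 2024. The article does not settle which visits were still to come.

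**Conclusion.** The point holds in conditional form. The two-visit schedule is unambiguous in Table 1. If all facilities are trained by FU3, as the text implies but does not state, the effect of training versus none on the CCPAI and Jefferson scales is confounded with calendar time and reduces to a before/after comparison (rank 12 of 13). If one to three arms are still untrained then, the effect is estimable with roughly 3 to 7 times the variance of a four-visit schedule, given the assumed 4/4/3 rollout and independent residuals between visits within an arm.

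Severity is moderate and confined to two secondary endpoints. The primary incident count, recorded continuously, is unaffected. So are the four-visit scales, including burnout, which appears in the same Discussion sentence.

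**What to change.** Mark both scales at FU1 and FU2 in Table 1, collect them in the interviews already held for the other scales, and analyse them with period effects in the same way. The cost is a few more questionnaire minutes per interview, with no additional visits. If FU1 has passed but FU2 has not, adding FU2 alone is still worthwhile.

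If data collection is complete, report both endpoints as uncontrolled before/after comparisons and qualify the Discussion's expectation of increased confidence and empathy. This costs only wording.

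In either case, state each arm's training, refresher and board status at FU3, and at which visits the shorter arms complete these two scales.

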### Recruitment {15}

The research study team will invite potential HCWs in DRC and junior medical doctors in Baghdad from selected sites to participate in the study. A designated contact person will collaborate throughout the project to ensure the sustainability of recruitment and communication between clusters and their organizational levels. In Iraq, within each site, junior doctors will be recruited from the most exposed wards. Each HCW will be assigned a unique ID number.

## Assignment of interventions: allocation

### Sequence generation {16a}

The study statistician will perform the randomization of health facilities to receive the intervention at pre-planned steps and will establish the random order of the allocation sequence through computer-generated random numbers.

